# A randomised, multi-centre, prospective, double blind pilot-study to evaluate safety and efficacy of the non-absorbable Optilene^® ^Mesh Elastic versus the partly absorbable Ultrapro^® ^Mesh for incisional hernia repair

**DOI:** 10.1186/1471-2482-10-21

**Published:** 2010-07-12

## Abstract

**Background:**

Randomised controlled trials with a long term follow-up (3 to 10 years) have demonstrated that mesh repair is superior to suture closure of incisional hernia with lower recurrence rates (5 to 20% versus 20 to 63%). Yet, the ideal size and material of the mesh are not defined. So far, there are few prospective studies that evaluate the influence of the mesh texture on patient's satisfaction, recurrence and complication rate. The aim of this study is to evaluate, if a non-absorbable mesh (Optilene^® ^Mesh Elastic) will result in better health outcomes compared to a partly absorbable mesh (Ultrapro^® ^Mesh).

**Methods/Design:**

In this prospective, randomised, double blind study, eighty patients with incisional hernia after a midline laparotomy will be included. Primary objective of this study is to investigate differences in the physical functioning score from the SF-36 questionnaire 21 days after mesh insertion. Secondary objectives include the evaluation of the patients' daily activity, pain, wound complication and other surgical complications (hematomas, seromas), and safety within six months after intervention.

**Discussion:**

This study investigates mainly from the patient perspective differences between meshes for treatment of incisional hernias. Whether partly absorbable meshes improve quality of life better than non-absorbable meshes is unclear and therefore, this trial will generate further evidence for a better treatment of patients.

**Trial registration:**

NCT00646334

## Background

### Rationale

70.000 incisional hernia repairs were performed in Germany in 2006 [1]. Incisional hernias can cause serious complications such as incarceration or strangulation, resulting in substantial costs for further treatment (~ 128 Million €). Optimal treatment has not yet been defined [2,3].

Currently, the surgeon usually implants a mesh to reinforce the abdominal wall. The use of a mesh prosthesis for incisional hernia repair results in a lower recurrence rate than suture repair [4-11]. Creating a tension free repair with a mesh reduces the recurrence rate to 5-10%. Studies performed by Israelsson et al. in 2006 [12] and Kingsnorth et al. in 2004 [13] showed that the sublay technique seems to result in a lower recurrence rate (3-7%) compared to the onlay technique (12-19%). In order to achieve a sufficient reinforcement of the abdominal wall, the mesh should overlap the defect more than 5 cm in all directions [13-15]. Several meshes are available which differ in material, textile structure, pore size, weight, elasticity, tissue reaction, biocompatibility, and absorption [16-22]. Patients react differently to the mesh and the materials cause different complications such as seromas, chronic pain, and infections [14,15,19,23,24].

### Purpose

The aim of this study is to evaluate the safety and efficacy of the Optilene^® ^Mesh Elastic manufactured by B|Braun Aesculap compared to, the Ultrapro^® ^Mesh by Johnson&Johnson. Surgeons currently use both meshes to repair incisional hernias [25-27]. The two meshes have large pores based on polypropylene. Optilene^® ^Mesh Elastic is made of pure polypropylene and is not absorbable. Ultrapro^® ^is a partly absorbable mesh (polypropylene plus polyglecaprone, table 1).

**Table 1 T1:** Comparison of the two meshes

Characteristics	Ultrapro	Optilene Mesh Elastic
Material	PP & PG (~ 1:1)	PP
Filament Structure	Monofil	Monofil
Construction	Knitted	Knitted
Weight after absorption of PG	65 g/m^2^ 28 g/m^2^	48 g/m^2^
Thickness	0,59 mm	0,55 mm
Pore Size	1.9 - 2.2 mm (min.- max.)	2.9 - 3.2 mm (min.-max.)
Absorption	partly absorbable	non-absorbable
Suture pull out test, lengthwise	33 N	33 N
Suture pull out test, crosswise	31 N	44 N

PP: Polypropylene, PG Polyglecaprone, N: Newton

## Methods/Design

### Study objectives

The primary objective of the study is to compare the physical functioning score from the SF-36 questionnaire 21 days after insertion of either an Optilene^® ^Mesh Elastic or an Ultrapro^® ^Mesh. Secondary objectives include the evaluation of the patients' daily activity, pain, wound assessment determined on several occasions during the observation time, the incidence of specific post-surgical complications and safety.

### Study design

The study is a prospective, randomised, patient and observer blinded study. It is conducted in six centres in Germany. In total eighty patients with incisional hernia meeting the specific inclusion criteria will be randomised and followed for six months thereafter (table 2 and figure 1). Patients who prematurely terminate participation in the study will not be replaced.

**Table 2 T2:** Tabular overview of the visits

	Visit 1 Pre- Surgery^1^	Visit 2 Surgery 0 Day	Visit 3 Release	Visit 4 Clinic 21 Days	Visit 5 Telephone 4 Months	Visit 6 Clinic 6 Months^2^
Patient information	X					

Informed Consent	X					

Demographics incl. employment status and home activities	X					

Body weight	X					X

Inclusion/Exclusion	X					

Medical history incl. history hernia	X					

Determination of potential risk factors	X					

Clinical examination	X					X

Concomitant medication	X	X^3^	X	X	X	X

General health status	X			X		X

SF-36	X			X		X

Daily activity questionnaire	X			X		X

Intra-operative details		X				

Adverse Events		X	X	X	X	X

Wound assessment			X	X		X

Seroma formation (sonography if indicated)			X	X		X

Pain score	X		X	X		X

Study termination						X

1) to be performed within 6 weeks before visit 2

2) or prematurely

3) concomitant medication except medication routinely given during a surgery and anaesthetic drug

**Figure 1 F1:**
[figure not shown]
**Flow-chart of the trial**.

### Study population

Female or male patients over 18 years old undergoing an elective repair for a midline incisional hernia are eligible for participation (table 3).

**Table 3 T3:** Eligibility

Inclusion Criteria	Exclusion Criteria
Patient is female or male and ≥ 18 years old	Patient participates simultaneously in an investigational drug or medical device study
Female patients are incapable of pregnancy or must be using adequate contraception and are not in lactation	Patient has an acute incarcerated hernia Patient had a previous mesh repair at the same site
Patient has only a vertical aponeurotic incision	Enterotomy to be performed during hernia repair at Visit 2
Patient has an incisional hernia with a hernia size ≥ 3 cm	Patient is on anti-coagulation therapy
Patient is capable to understand and to follow the instructions	Patient is known or assessed to be non-compliant
Written informed consent is available	Patient must not get any additional surgical treatment at the same time (e. g. cholecystectomy)
Patient had no mesh implantation at the same site during a previous operation	Patient is immune incompetent (e. g. chemotherapy)

### Ethics and informed consent

The commercial regulatory authority Hannover gave its positive approval in February 2006. For the two centres in Heidelberg the Ethics Committee of the University of Heidelberg Medical School approved the final protocol on the 8^th ^Oktober 2007 and on 20^th ^November 2007. A central ethics approval was also obtain from the International Ethics Committee of Freiburg on the 4^th ^May 2009. Written informed consent will be obtained from all patients participating in the trial. The study is conducted in accordance with the principles of the Good Clinical Practice (GCP) guidelines, the Declaration of Helsinki, and the European Standard EN ISO 14155 Parts I and II (2003), "Clinical Investigation of Medical Devices for Human Subjects".

### Randomisation and blinding

Patients will be randomised by opening sealed, opaque envelopes containing the mesh to be implanted. The sponsor will prepare envelopes with a balanced distribution of meshes, according to the randomisation plan. The meshes will be assigned to patients in each centre in chronological order. Neither the patient nor the observer will have access to the documents indicating mesh distribution. The surgeon should not be the observer of outcomes in this clinical trial. Therefore, at least two different persons per centre are involved in this study, one who performs the surgery and the other one conducting the follow-up examinations. Together with the meshes the study centres receive emergency envelopes with the information of treatment allocation. The sponsor has to be contacted before breaking the code for a given patient. In case of opening the envelope, time, date, name of the person opening and the reason for opening the envelope are to be documented on that envelope and in the corresponding CRF.

### Intervention

In order to minimise bias and to assure parity in treatment for all patients, the following standardised procedures were implemented.

The operation is initiated with a vertical median incision. After classification of the hernia according to Schumpelick, a space is created between both posterior sheaths and the rectus muscle. The posterior fascia is closed using a running monofilament non-absorbable suture. The mesh is placed in sublay position between the posterior rectus sheath and the rectus muscle with an overlap of the defect of 5 cm in all directions (figure 2). Whereby the largest elasticity of the mesh is in vertical direction. The mesh is then fixed to the posterior fascia using a single knot technique every 3 cm with monofilament, non-absorbable suture material. The closure of the midline anterior rectus sheath is conducted with a continuous running technique using monofilament, non-absorbable sutures with a 4:1 ratio (suture length: incision length). Two Redon drains are placed close to the mesh. The skin is closed with tacks and an abdominal bandage is applied.

**Figure 2 F2:**
[figure not shown]
**Sublay technique for open incisional hernia repair**.

### Data collection and examinations

The investigator will collect data in a CRF about the patient and perform six examinations (table 2). CRF are paper-based and will be entered into a database by two persons independently applying plausibility checks. Queries raised during data base input will be clarified with the investigators.

### Questionnaires

The SF-36 Health Survey is a validated instrument to measure health status and patients are requested to complete the questionnaire before surgery, on day 21 after intervention and six months postoperatively.

### Documentation during and after surgery

During surgery, the investigator documents the size of the incision, the device and the material used for fixation, intra-operative complications, classification of the defect, and the size of the overlap of the mesh. The observer will record wound assessment, daily activity and pain as secondary endpoints (table 2).

### Safety aspects

The investigator has to document adverse events and serious adverse events on the appropriate form of the CRF which occur in the abdomen. Serious adverse events occurring during the study or within two weeks after discontinuation have to be reported to the sponsor within 24 hours of becoming aware of the event. It is the responsibility of the principal investigator at each centre to inform the local ethics committee of SAEs occurring at the centre according to local requirements.

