### Sample size and statistical analysis

The primary efficacy endpoint is the change of SF 36 PCS between baseline and average of SF 36 PCS 21 days after intervention. The primary efficacy analysis will be conducted in the intention-to-treat population and applies a fixed effect linear model adjusting for age, BMI and SF 36 PCS before. Level of significance is set at 5% (two-sided).

Due to the lack of any empirical data for the primary endpoint in the population under investigation, there is substantial uncertainty with respect to overall rate and treatment effect to be expected. As a consequence, the assumptions to be made for sample size calculation are highly uncertain and therefore, the study is performed as a pilot randomised trial with 80 patients.

Secondary endpoints are level of function and daily activity, seroma formation, wound assessment, neuralgias, time to return to work and to normal activities, the patient's rating of pain, analgesic consumption and other SF-36 scores during 6 months after surgery. These data will be analysed descriptively. No confirmatory statistical testing will be done with regard to secondary endpoints. Details of the analysis of secondary outcome parameters will be documented before database lock in the analysis-plan. The safety assessments, including adverse events and serious adverse events, will be analysed descriptively.

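### CRF documentation of AEs and SAEs is limited to abdominal events, while the safety aim, visit schedule, SAE reporting and safety analysis carry no such limit

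*Protocol article*

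**What the plan says.** The Safety aspects section of the protocol article opens with the documentation rule: "The investigator has to document adverse events and serious adverse events on the appropriate form of the CRF which occur in the abdomen". It then gives a reporting rule with no body-site limit: "Serious adverse events occurring during the study or within two weeks after discontinuation have to be reported to the sponsor within 24 hours" of the site becoming aware. The principal investigator must also "inform the local ethics committee of SAEs occurring at the centre according to local requirements", again without a limit.

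The other relevant statements are equally general. The Purpose section begins "The aim of this study is to evaluate the safety and efficacy". Study objectives lists, among the secondary objectives, "the incidence of specific post-surgical complications and safety". Table 2 has one unqualified row for adverse events, marked at Visits 2 to 6. On analysis, the statistical section says: "The safety assessments, including adverse events and serious adverse events, will be analysed descriptively". On where the data come from, Data collection and examinations says: "CRF are paper-based and will be entered into a database by two persons independently applying plausibility checks".

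**The concern.** The form that feeds the trial database has a narrower scope than the aim and analysis it must serve. After open abdominal wall surgery, a pneumonia, thromboembolic event, cardiac event or systemic infection is not in the abdomen. If non-serious, it need not be written down on any AE form. If serious or fatal, it goes to the sponsor but is not required on the CRF.

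The completeness of the by-mesh safety tables is at stake. Tables drawn from the CRF form could be read as showing all adverse events when they show abdominal ones only, and their SAE count could disagree with the sponsor's file. The rule also makes recording depend on a judgement about location, which is unclear for general reactions or systemic infections.

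**Working it through.** No arithmetic applies. The article gives no expected rate of adverse events, abdominal or other, so the number falling outside the rule cannot be derived. The check is a comparison of scope.

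**1. Scope of each statement**

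| Statement | Place in the protocol article | Limited to the abdomen? |
|---|---|---|
| Documentation of AEs and SAEs on the CRF | Safety aspects, first sentence | Yes |
| SAE report to the sponsor | Safety aspects, second sentence | No |
| SAE information to the local ethics committee | Safety aspects, third sentence | No |
| Adverse events at Visits 2 to 6 | Study design, Table 2 | No |
| Safety as an aim | Purpose | No |
| Safety as a secondary objective | Study objectives | No |
| Descriptive analysis of AEs and SAEs | Sample size and statistical analysis | No |

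**2. Reading of the first sentence.** The word order is awkward, but the closing clause can only sensibly describe the events. It covers both AEs and SAEs.

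**3. Is safety meant to be narrow?** Study objectives names specific post-surgical complications and safety as separate items. Wound assessment and seroma have their own rows in Table 2. That suggests safety was meant to reach beyond local events, and nothing in the article narrows it.

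**4. Route of each type of event under the text as written**

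- Abdominal, non-serious: CRF form, then database.
- Abdominal, serious: CRF form, then database, and also the sponsor.
- Non-abdominal, serious: sponsor and ethics committee; not required on the CRF form.
- Non-abdominal, non-serious: no stated route. Concomitant medication is recorded at every visit, so a drug given for such an event could appear without a matching AE.

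**5. Consequence for the SAE counts.** The SAEs required on the CRF are a subset of those the sponsor must receive. The two sets are equal only if no SAE occurs outside the abdomen or if sites record more than the rule asks. The section on trial organization puts the database and biostatistics with the CRO, while SAE reports go to the sponsor. The article describes no step that brings the two together.

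**The case against.** The case for leaving the text alone has several parts.

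- *Both rules can be followed at once.* This stands. One sentence governs the CRF and the next governs reporting. A reader might infer a contradiction, but there is none: following both gives two SAE sets of different scope.
- *Serious events are not lost.* This also stands. A reader might infer that all non-abdominal events disappear, or that total SAEs per mesh could never be stated. The documents do not support either reading. Such SAEs reach the sponsor within 24 hours, and the sponsor prepares the mesh envelopes to the randomisation plan, so they could be counted by mesh. The article does not say that sponsor reports are kept out of the analysis; it only gives no route for them.
- *An abdominal focus may be deliberate.* Both meshes are already in use, and the complications that the article links to mesh are mainly seroma, pain and infection. That could justify a narrow scope, but the article does not say so and does not narrow its aim or analysis to match.
- *The filter does not bias the comparison.* A reader might infer that it favours one mesh. The documents give no support for this: the rule is the same in both arms, and patient and observer are blinded. The problem is completeness.
- *A journal article condenses.* This excuses missing detail, such as the reconciliation procedure. It does not excuse a stated restriction that is narrower than the stated analysis. Nor can an analysis plan recover non-serious events that were never recorded.

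**Conclusion.** The concern holds as a mismatch of scope. The CRF rule is narrower than the safety aim, the visit schedule, the SAE reporting rules and the planned analysis. Non-serious events outside the abdomen have no stated place in any safety record. Non-abdominal SAEs and deaths are held by the sponsor but are not required in the CRF-fed database, so the two SAE sets can differ.

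Severity is moderate. Safety is a secondary objective, analysed descriptively, in a pilot of 80 patients, and the analysis of the primary endpoint is untouched. The conclusion rests on two assumptions: that sites follow the first sentence literally, and that the safety tables are drawn from the CRF database. The second is the natural reading of the data collection section, but the article does not state it outright.

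**What to change.** 1. Remove the abdominal restriction for SAEs. Enter every SAE and death in the CRF database whatever the body site, and reconcile that database with the sponsor's SAE file before lock. SAEs already reported to the sponsor can be entered retrospectively.
2. Record all AEs at Visits 2 to 6, as Table 2 already schedules, with a flag for abdominal or mesh-related events. Tabulate the flagged events as a pre-defined subset, which keeps the mesh-specific focus.
3. Where non-serious non-abdominal AEs can no longer be recovered, label the AE tables as abdominal events only and limit the safety conclusion to match.

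The third step matters because of the dates in the article. The last randomisation was expected in November 2009, and six months of follow-up takes that patient to May 2010. Completion was estimated for June 2010, and the article appeared on 12 July 2010. On that timetable the visits were essentially over, so for most patients labelling is the realistic remedy for non-serious events, while steps for SAEs remain feasible until lock.

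The cost is a change of wording in the protocol and CRF instructions, a few more AE lines per patient where collection is still possible, and one reconciliation step. Abdominal events remain available for separate tabulation.

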### Sample size and statistical analysis

The primary efficacy endpoint is the change of SF 36 PCS between baseline and average of SF 36 PCS 21 days after intervention. The primary efficacy analysis will be conducted in the intention-to-treat population and applies a fixed effect linear model adjusting for age, BMI and SF 36 PCS before. Level of significance is set at 5% (two-sided).

Due to the lack of any empirical data for the primary endpoint in the population under investigation, there is substantial uncertainty with respect to overall rate and treatment effect to be expected. As a consequence, the assumptions to be made for sample size calculation are highly uncertain and therefore, the study is performed as a pilot randomised trial with 80 patients.

Secondary endpoints are level of function and daily activity, seroma formation, wound assessment, neuralgias, time to return to work and to normal activities, the patient's rating of pain, analgesic consumption and other SF-36 scores during 6 months after surgery. These data will be analysed descriptively. No confirmatory statistical testing will be done with regard to secondary endpoints. Details of the analysis of secondary outcome parameters will be documented before database lock in the analysis-plan. The safety assessments, including adverse events and serious adverse events, will be analysed descriptively.

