### Current status

The first investigator meeting was held on 21^st ^December 2005 in Tuttlingen, Germany. The study protocol for this trial was completed on 19^th ^January 2006. In February 2006, following completion of contracts the first three centres (Hannover, Aschaffenburg, Northeim) were initiated, the first patient was recruited in July 2006. Due to slow accrual of patients three other centres (University of Heidelberg, University of Mannheim, Salem Hospital in Heidelberg) were initiated in December 2007. It is expected that the last patient will be randomised in November 2009. The study is estimated to be completed in June 2010.

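### If meshes are balanced within centre, as the allocation procedure suggests, the primary model should include centre; leaving it out makes the test mildly conservative

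*Protocol article*

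**What the plan says.** Three parts of the protocol article bear on this point.

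- **Allocation** (*Randomisation and blinding*): "The sponsor will prepare envelopes with a balanced distribution of meshes, according to the randomisation plan". Then: "The meshes will be assigned to patients in each centre in chronological order". The article does not use the words stratified or blocked, gives no block size, and does not say at which level the distribution is balanced.
- **Centres** (*Study design*): "It is conducted in six centres in Germany". *Current status* adds that the first patient was recruited in July 2006 and that three of the six centres were initiated only in December 2007: "Due to slow accrual of patients three other centres".
- **Primary analysis** (*Sample size and statistical analysis*): the endpoint is a change in SF-36 PCS from baseline to day 21, tested at a two-sided 5% level in the intention-to-treat population. The analysis "applies a fixed effect linear model adjusting for age, BMI and SF 36 PCS before". Only the details of the secondary analyses are deferred to the analysis plan, so the primary covariate list reads as settled.

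On size, "the study is performed as a pilot randomised trial with 80 patients". No effect size, standard deviation or power is given.

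**The concern.** When allocation is balanced within a factor, the treatment comparison is largely free of that factor's variation. A model that omits the factor does not know this. It leaves the between-centre variance in the residual and reports a standard error larger than the true sampling variation of the estimate. The usual rule is therefore to analyse by the groups within which one randomised.

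Centre could plausibly matter here. The article requires at least two people per centre, one to operate and one to follow up, so surgeon and observer both vary with centre. Calendar time does too: July 2006 to December 2007 is 17 months. None of these is carried by age, BMI or baseline PCS. At stake is some precision in a trial of 80 patients in which those who leave early are not replaced.

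**Working it through.** **Is there a planned figure to reproduce?** No. The 80 patients are not derived from a power calculation. For scale only, with 40 per arm (1:1 assumed) and two-sided 5%, the difference detectable with 80% power is (1.960 + 0.842) × √(2/40) = 2.802 × 0.2236 = 0.63 SD. That value serves below as an assumed true effect.

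**Inputs.** From the article: N = 80, six centres, alpha 0.05 two-sided, three covariates. Assumed: the ICC (ρ, the between-centre share of the outcome variance left after the covariates), the centre sizes, the block size, the 0.63 SD effect, and all 80 patients contributing data.

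**Rough formula under exact balance within equal centres.** The true variance of the estimate is proportional to 1 − ρ. The model without centre estimates a residual variance of about (1 − ρ) + ρ × 5/6 = 1 − ρ/6, since six centres carry 5/6 of ρ as observed spread. So

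reported SE / true SE ≈ √[(1 − ρ/6)/(1 − ρ)].

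- ρ = 0.02: √(0.9967/0.98) = 1.01
- ρ = 0.05: √(0.9917/0.95) = 1.02
- ρ = 0.10: √(0.9833/0.90) = 1.05
- ρ = 0.20: √(0.9667/0.80) = 1.10

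**Simulation, permuted blocks of 4 within centre.** There were 6,000 trials per setting. The analysis was least squares on treatment and three covariates, with and without five centre indicators. Centres were near-equal (14/14/13/13/13/13).

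| ICC | Power without → with centre | Type I error without centre | Mean SE / true SD, without centre |
|---|---|---|---|
| 0 | 77.6% → 77.4% | 4.6% | 0.99 |
| 0.02 | 77.9% → 78.0% | 4.8% | 1.01 |
| 0.05 | 78.4% → 79.4% | 4.3% | 1.00 |
| 0.10 | 79.2% → 81.2% | 4.0% | 1.04 |
| 0.20 | 80.6% → 85.3% | 3.7% | 1.07 |

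Simulation error is about 0.5 points for power and 0.3 points for type I error. Unequal centres (30/20/12/8/6/4) give nearly the same power: 77.3% → 76.8% at ICC 0, 79.8% → 82.0% at 0.10 and 80.9% → 85.3% at 0.20.

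**Simulation, even centre sizes (20/16/14/12/10/8), balanced within centre,** 8,000 trials per setting. Power is 79.6% → 80.7% at ICC 0.05, 80.6% → 82.9% at 0.10 and 81.8% → 87.1% at 0.20. At 0.20 the standard error is 0.220 without centre and 0.201 with it (0.220/0.201 = 1.09), and type I error without centre is 3.4%. The 7% and 10% figures at ICC 0.20 therefore reflect incomplete blocks against near-exact balance, and partly the choice of comparator (true SD of the estimate, or SE of the model with centre).

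**Simulation, balance only over the whole trial.** The standard error without centre is not overstated (ratio 0.97 to 1.00). Change in power from adding centre, near-equal and unequal sizes:

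| ICC | Near-equal | Unequal |
|---|---|---|
| 0 | −2.8 points | −2.5 points |
| 0.02 | −2.4 | −2.0 |
| 0.05 | −0.9 | −1.5 |
| 0.10 | +0.7 | +0.5 |
| 0.20 | +3.5 | +4.9 |

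The level at which allocation is balanced thus decides whether adding centre is nearly free or a trade-off.

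**The case against.** The strongest objection is that balance within centre is inferred. The sentence on balanced envelopes names no level, the sentence on chronological order describes only the order of use, and the randomisation plan is not shown. This stands, and the last table shows that the conclusion depends on it. The point can only be put conditionally.

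A second objection is that no centre effect is documented. Baseline PCS, age and BMI absorb some of the case mix, and the *Intervention* section standardises the operation so that patients are treated alike. This stands too: the ICC of 0.20 that produces the larger loss is an assumption.

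A third is that this is a condensed article, that its covariate list is not marked as complete, and that an analysis plan may add centre. This is weaker, because the article states the primary covariates and defers only the secondary details.

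A reader might also infer that the trial wastes planned power. The article does not support this: it is a pilot without a power target, so there is no planned figure to fall short of. Nor does the point reach the secondary endpoints, which are to be analysed descriptively without confirmatory tests.

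**Conclusion.** The point holds in conditional form and is of modest size. If allocation is balanced within centre, and centre remains prognostic after the three stated covariates, the stated primary model reports a standard error that is somewhat too large and a test that is conservative. Under the assumed ICCs, nothing is lost at 0 to 0.02 and about 1 to 2 points of power at 0.05 to 0.10. At 0.20 the loss is about 4 to 5 points, with a standard error roughly 7 to 10% too wide.

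A reader might take the omission to make the primary test invalid or the estimate biased. It does neither. Under balance within centre, type I error stays at or below the nominal level within simulation error (down to about 3.4 to 3.7% at ICC 0.20), and omitting centre does not bias the treatment estimate. No figure in the article is wrong. The reason to act is that, under balance within centre, including centre costs almost nothing if centre is irrelevant and helps if it is not.

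**What to change.** Confirm from the randomisation plan whether allocation is balanced by centre, and state it. If it is, add centre to the primary linear model as a fixed factor. Set a rule before database lock for very small centres: either pool them by a stated criterion or use a random centre intercept. Alternatively, justify leaving centre out.

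If balance holds only over the whole trial, say so. Centre is then a judgement: in the simulations it costs about 1 to 3 points of power at ICC 0 to 0.05, is about neutral at 0.10 and gains about 3 to 5 points at 0.20.

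The cost under balance within centre is one sentence in the analysis plan and 5 degrees of freedom. The residual falls from 80 − 5 = 75 to 70 if all patients are analysed. If centre does not matter, power falls by about 0.2 points with near-equal centres and 0.5 with unequal ones, both within simulation error. Trial conduct is unaffected.
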